## Assignment of interventions: blinding

### Who will be blinded {17a}

Trial participants, doctors, care providers, outcome assessors and data analysts will be blinded. After initial screening, an investigator will log onto the Central Randomization System to enter demographic information of an enrolled patient to produce a random number application. A designated individual will then apply for a drug package number and dispense the drug when the package number is consistent with the one recorded in the database. When all data were analysed completely, unblinding of experimental groups was conducted under the supervision of the Contract Research Organization and the Trial Committee.

### Procedures for unblinding if needed {17b}

All serious adverse events (SAEs) are to be reported within 24 h of the site investigator becoming aware, and a full report is to be filled to the sponsor and the State Food and Drug Administration (SFDA). The ethics committee of the pharmaceutical affairs of ONET will conduct an investigation to confirm the causes of an SAE, decide whether the participant can continue with study medication and whether the need to apply to the organization for emergency unblinding.

## Data collection and management

### Plans for assessment and collection of outcomes {18a}

Data management will be performed by the Stemexcel Technology company, Beijing, China [24], using specially designed case report forms (CRFs) on a DAS for EDC system. The table illustrates the schedule and nature of the data collection required during the study period.

### Plans to promote participant retention and complete follow-up {18b}

Treatment compliance is monitored through pill counts and regular contact with participants, with instructions to adjust medication dosage at weekly outpatient clinic visits. Each patient is given a concise diagram of the trial process with the following details: when the patient comes in to collect their medication, when and where the patient will be scheduled for tests and what the telephone number of the hospital emergency contact is.

### Data management {19}

All CRFs are first examined and verified by 2 investigators at each study site, before a data manager undertakes further central checks and confirmation or correction of any errors or inconsistencies via a clinical monitor before finalization of the data. The CRF will be inspected by an assigned person at regular intervals throughout the trial in order to verify adherence to the protocol. Data lock occurs when all subjects have completed their follow-up and there are no outstanding data queries. All computerized forms are electronically signed (by use of the unique password) by authorized study staff; all changes made following the initial entry have an electronic dated audit trail. The paper-based CRF will eventually be converted into an electronic CRF for statistical and management purposes.

### Confidentiality {27}

Every precaution is taken to respect the privacy of participants in the conduct of the study. Only de-identified data will be used for statistical analysis and the publication of results to maintain confidentiality. Only the subjects’ numbers instead of names or admission numbers can be used for identification in all the documents submitted to the sponsor. While the grouped table recording correspondence of the subjects’ names and numbers should be kept properly and confidentially by the Contract Research Organization, and not be submitted to the sponsor.

### Plans for collection, laboratory evaluation and storage of biological specimens for genetic or molecular analysis in this trial/future use {33}

Laboratory tests are carried out according to the standard blood collection procedures of Tianjin Medical University General Hospital. All specimens are not retained but are directly reported by the clinical laboratory

## Statistics methods

### Statistical methods for primary and secondary outcomes {20a}

The primary analysis will be performed according to the intention-to-treat (ITT) principle, comprising all randomized participants. A per-protocol analysis will also be undertaken for all participants who have taken at least one dose of the trial medication and complete at least one follow-up assessment. The description of indicators will be by number of cases (and percentages) for categorical variables, and mean (standard deviation) or median (interquartile range) for continuous variables. The chi-square test and logistic regression with adjustment for site, age, sex and baseline haematoma volume will be adopted for the comparison of the primary outcome between the treatment groups. For secondary outcomes, Student’s *t*-test or non-parametric Wilcoxon tests will be performed for continuous outcomes and the chi-square test for dichotomous outcomes. Ordinal logistic regression will be used for the analysis of the shift in the full range of scores on the mRS. All statistical tests are two-sided, with a *p*-value < 0.05 indicating statistical significance. All analysis will be conducted using SAS 9.4 (SAS Institute Inc., USA).

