#### Intervention description {11a}

All patients are to take oral 20 mg atorvastatin (one tablet) daily for 4 weeks as a standard of care. Those patients allocated to the intervention group will receive extra dexamethasone with a dose of 0.75 mg per once for three times daily during the first 14 days, and thereafter, the dose will be reduced to twice daily for 7 days, and then once a day for another 7 days. Thus, a total of 560 mg atorvastatin and 47.25 mg dexamethasone will be taken for 28 days. Patients assigned to the control group will receive the same open atorvastatin regimen but also placebo dexamethasone in the same schedule over 28 days.

At the end of the 28-day treatment period, haematoma volume will be re-evaluated on repeat CT scans and the following treatment regimens considered: (i) if the haematoma has resolved or present in a very small amount, the investigator can stop study treatment and only conduct follow-up observations until 180 days; (ii) if the haematoma appears reduced but still present, the investigator can decide either to consider ceasing medication and observing considering early surgery; (iii) if there is no obvious change in the haematoma, two researchers can jointly determine whether to continue conservative management or undertake surgery; and (iv) if the amount of haematoma is increased, the patient may undergo surgery.

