#### Criteria for discontinuing or modifying allocated interventions {11b}

Eligible patients are centrally randomized in a 1:1 allocation ratio to intervention (atorvastatin combined with low-dose dexamethasone) and control (atorvastatin combined with matching placebo) groups using a blocked randomization method via a data acquisition system for electronic data capture (DAS for EDC, version 5.0) developed by Stemexcel Technology Co. Ltd., Beijing.

If a participant develops any form of neurological deterioration (e.g. altered level of consciousness) that is suggestive of expansion of the haematoma, they may be admitted to the hospital for assessment and treatment until their symptoms are relieved or resolve. If surgery is undertaken for a deteriorating patient, the randomized oral study medication is to be resumed as soon as possible after the operation until the end of the planned 28-day treatment period.

The patient has the right to refuse treatment at any time or to withdraw completely from the trial. The investigator can also ask the patient to withdraw from the trial, including (1) the compliance of the subjects was poor and the scheme was violated, (2) unacceptable adverse reactions/serious adverse events occur, (3) subjects experienced serious complications during the trial and urgent measures were required, (4) the subject withdraws from the clinical trial or withdraws the informed consent form and (5) other special circumstances.

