#### Strategies to improve adherence to the intervention {11c}

Treatment compliance is monitored through pill counts and regular contact with participants, with instructions to adjust medication dosage at weekly outpatient clinic visits. All the patients were treated in an outpatient setting and received 7-day supplies of the medication in seven individual packages. They returned the empty packages at the end of each week to exchange them for the next week’s supply, until the treatment ended.

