#### Relevant concomitant care permitted or prohibited during the trial {11d}

Most participants are treated as outpatients receiving conventional and standard cares such as rest and pain relief. Family members are responsible for monitoring the patients for progress in neurological symptoms such as worsening headaches. If a patient is reported to have worsening symptoms, he or she will be further evaluated by two attending physicians for neurological deficits. These patients may be admitted during the trial for the treatment of progressing neurological deficits and discharged when their symptoms are relieved significantly.

Within 72 h prior to treatment, CT, routine blood test, coagulation, blood glucose and biochemical analysis were rechecked before enrolling into the group, as well as neurological assessment. At the end of 2 weeks and 4 weeks, routinely check blood test, coagulation, blood glucose and biochemical analysis and re-evaluate neurological function. CT scans are performed at end of 2 weeks, 4 weeks and 3 months. mRS and ADL-BI were scored before treatment and at the end of 4 weeks, 3 months and 6 months.

Each patient receives an in-person clinical assessment at an outpatient clinic by two attending neurosurgeons who are kept blind to the treatment allocation, every 2 weeks during the 28-day treatment duration, and then each month thereafter until 180 days post-randomization.

Anticoagulants (warfarin or new oral anticoagulants) are prohibited. Antiplatelet drugs (aspirin, clopidogrel) or Xuesaitong (traditional Chinese medicine for activating blood circulation) can potentially interfere with haematoma absorption and are not recommended during the treatment. However, these patients will not be exclusively excluded from the trial participation. The following drugs may potentially interact with statins and/or cause adverse events and will not be recommended during the treatment: red yeast rice, erythromycin, fibrates, cyclosporin, macrolide antibacterials, azole anti-fungals, tacrolimus, gemfibrozil, troglitazone and itraconazole.

The use of other medications is recorded in the case report form (CRF), including their name, dose and duration of treatment. Any change in haematological and biochemical markers, such as liver function tests, and side effects, such as myalgia, constipation and other possible drug-related symptoms, will be recorded. All details of any treatment during the 180-day study period are recorded.

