### Implementation {16c}

Study medication is provided free of charge to participants: atorvastatin by Pfizer Inc. and dexamethasone by Tianjin Pacific Pharmaceutical Co. Ltd. (Tianjin, China). The placebo dexamethasone, which is composed of dextrin and with the same weight and appearance as dexamethasone, is made by Tianjin Pacific Pharmaceutical Co. Ltd. (Tianjin, China), which has a certification of Good Manufacturing Practice (GMP) for pharmaceutical products issued by the State Food and Drug Administration of China.

Study medication is packed identically and labelled ‘for clinical study use only’ with a packaging number, verification code, dosage, specifications, storage, batch number, duration of usage and manufacturer. A statistician and staff independent of the study research team oversee the packaging of the study medication, with the use of a package number and drug verification code on the tag. Each participant is allocated a unique number to be applied to a drug package number for dispensing and consistency in the database.

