### Methods in analysis to handle protocol non-adherence and any statistical methods to handle missing data {20c}

The full analysis set (FAS) included the patients who took the drug at least once and had the primary therapeutic evaluation data at baseline. In the FAS, missing data from the 4 weeks of treatment were replaced with the last available data, in accordance with the last observation carried forward (LOCF) principle. If more than 5% of patients have a missing primary outcome, we will use multiple imputations for a sensitivity analysis.

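### The set labelled per-protocol is a modified intention-to-treat set: it drops only never-dosed and never-assessed patients, so it cannot check the result under adherence

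*Protocol article*

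**What the plan says.** In the protocol article, the section on statistical methods for primary and secondary outcomes {20a} makes ITT, with every randomized participant, the primary analysis. It adds a per-protocol analysis for "all participants who have taken at least one dose of the trial medication and complete at least one follow-up assessment". No other section defines that set.

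The section on non-adherence and missing data {20c} defines a third set: "The full analysis set (FAS) included the patients who took the drug at least once", with baseline data for the primary evaluation as the second condition.

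Other sections say what following the plan means:

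- Intervention description {11a}: "a total of 560 mg atorvastatin and 47.25 mg dexamethasone will be taken for 28 days".
- Strategies to improve adherence {11c}: "Treatment compliance is monitored through pill counts and regular contact with participants".
- Criteria for discontinuing {11b}: one ground on which the investigator may withdraw a patient is that "the compliance of the subjects was poor and the scheme was violated".
- Concomitant care {11d}: "Anticoagulants (warfarin or new oral anticoagulants) are prohibited", and "CT scans are performed at end of 2 weeks, 4 weeks and 3 months".

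**The concern.** A per-protocol analysis is read as the result in patients who substantially followed their assigned regimen. Here membership depends on one dose and one later assessment. It does not depend on pill counts, prohibited drugs or eligibility, nor on having the day-28 scan. The article states the rule in full, and it covers all participants who meet the two conditions. So this is a criterion fixed badly, not a detail left for an analysis plan; an analysis plan that added an adherence threshold under the same name would contradict it.

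What is at stake is interpretation. The hypothesis concerns the combination against atorvastatin alone, and the arms differ only in dexamethasone. If the ITT effect is smaller than planned, a reader will look to the per-protocol analysis to see whether poor dexamethasone adherence contributed. This set cannot answer that. If the two analyses agree, the agreement may be taken as confirmation under adherence when it mostly reflects the same patients being counted twice.

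**Working it through.** **1. The plan's own dose total.** From {11a}, the schedule is three doses a day for 14 days, two for 7 days and one for 7 days: 14×3 + 7×2 + 7×1 = 63 doses. At 0.75 mg each, 63 × 0.75 = 47.25 mg, which matches the stated total. One dose is 1/63 = 1.6% of the course.

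**2. The three sets side by side.**

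- ITT: all randomized.
- Full analysis set: at least one dose, plus baseline data.
- Per-protocol: at least one dose, plus one follow-up assessment.

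The last two differ only in the second condition. Neither uses adherence.

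**3. The rule against the protocol's own standards.**

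- Adherence: pill counts are collected, but the rule does not use them.
- Withdrawal for poor compliance: a patient withdrawn on this ground after one dose and one assessment still qualifies.
- Anticoagulants: prohibited, but taking one does not exclude a patient.
- Eligibility: a patient found not to meet the entry criteria still qualifies.
- Outcome data: any single follow-up assessment is enough. The primary outcome needs haematoma volume at day 28, and the rule does not ask for that scan.

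**4. Overlap with ITT.** The sample size section {14} allows 5% loss at 4 weeks: 0.05 × 240 = 12 patients. Suppose all 12 had no follow-up assessment at all. The set then holds 240 − 12 = 228. For nested samples with similar variance, the correlation between the two estimates is about √(228/240) = 0.97. Patients lost by 4 weeks may well have had an earlier assessment and would then stay in. Never-dosed patients would also leave, but the article gives no number for them.

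**5. What the set shows when patients stop early.** The article gives no non-adherence rate, so this is an assumed range. Let a fraction f of the combination arm stop dexamethasone almost at once and do as well as control. The 20-point planned effect becomes 20 × (1 − f):

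- f = 5%: 19.0 points
- f = 10%: 18.0 points
- f = 20%: 16.0 points

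The present per-protocol set keeps these patients, so it shows the same diluted figures as ITT. A set that required adherence would show 20.0, but only if stopping is unrelated to prognosis.

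**6. What an adherence-based set would risk.** The planned control rate is (48 + 20 + 9)/(81 + 30 + 12) = 77/123 = 62.6%. Assume 10% stop, in the combination arm only; that stoppers have good-outcome rate r and gain nothing; and that the true effect in the rest is 20 points. The adherent-set difference is (0.626 − 0.1r)/0.9 + 0.20 − 0.626. ITT gives 18.0 points whatever r is.

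- r = 40%: 0.651 + 0.20 − 0.626 = 22.5 points
- r = 50%: 0.640 + 0.20 − 0.626 = 21.4 points
- r = 80%: 0.607 + 0.20 − 0.626 = 18.1 points

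The adherent set can therefore overstate or understate the 20 points. Below about r = 45% its error exceeds the 2.0 points of dilution that it removes.

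**The case against.** The strongest reply is that little depends on this set. ITT is primary in a superiority trial, and the article ties no stopping rule and no sample-size term to the per-protocol analysis. Pill counts are collected, so adherence can be reported anyway. An adherence-based set brings selection bias of its own, as step 6 shows. All of this stands and limits the weight of the point. It does not make the stated rule fit its label.

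A reader might infer four stronger things that the document does not support:

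- *That the set removes no protocol violator.* It does exclude patients who were never dosed and those never assessed afterwards.
- *That the defect costs the trial power.* Non-adherence would lower the power of the ITT analysis, but that holds however the per-protocol set is defined, and redefining it recovers none.
- *That a patient with no dexamethasone at all qualifies.* This needs the undefined term trial medication to include atorvastatin. The implementation section {16c} points that way: "Study medication is provided free of charge to participants: atorvastatin by". But {11a} treats atorvastatin as open standard care for everyone, and reading the term as dexamethasone or its placebo is at least as natural.
- *That a patient qualifies at day 7 with no follow-up CT.* Table 1 has a day-7 visit, but {11d} sets the in-person neurosurgical assessments two weeks apart, so the first may coincide with the day-14 scan. Even then the rule requires no day-28 CT.

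**Conclusion.** The point holds as a mislabelled and poorly fixed supportive analysis set. The stated rule is a modified ITT rule: 1 of 63 doses and one assessment suffice, and dosed, assessed patients with poor adherence, prohibited anticoagulant use or eligibility violations remain. On the planning figure for loss, at least 228 of 240 patients would be shared with ITT and the estimates would correlate at about 0.97. That assumes the 5% loss covers everyone who leaves the set; never-dosed patients would lower it slightly. Agreement with ITT therefore says almost nothing about the effect under adherence.

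The primary analysis and its conclusion are untouched. The dilution figures in step 5 rest on assumed stopping rates; they show what the set fails to remove, not a loss that the set causes. The correction is worth making because it is cheap and prevents a misreading.

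**What to change.** Keep ITT as primary. Rename the present one-dose, one-assessment set modified ITT. Define a separate per-protocol set, labelled supportive, of patients who:

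- met the eligibility criteria in {10};
- reached a pre-specified minimum pill-count adherence to dexamethasone or placebo, counted up to surgery or death if either came first. At 80%, for example, 0.80 × 63 = 50.4, so 51 of 63 doses over the full course. The 80% is a convention, not a figure from the article, and the sponsor should choose the threshold;
- took no prohibited anticoagulant;
- had the day 28 ± 3 CT, or had surgery or died before it. Those with surgery or death count as failures.

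Fix membership at a blinded data review, and report exclusions by arm and reason.

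The cost is a short text change. Pill counts, medication records and scans are already collected, so no new data are needed for the 141 patients enrolled by November 2021. As a protocol change it follows the amendment route in {25}, through the sponsor, the centres and the ethics committee.

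The downside is selection. A patient who stops tablets because of deterioration or an adverse event fails the threshold before any surgery and is excluded. The new set can thus be biased in either direction, and it should support the ITT result, never replace it.

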### Participant timeline {13}

Baseline demographic and clinical features, including medical history, severity and type of neurological deficit and physical and biochemical results, are collected at the time of enrolment in the study. Treatment should be initiated immediately after randomization (Table 1). All background care should follow standard guideline recommendations for the management of CSDH in China which includes the withholding of anticoagulation and use of antiplatelet agents and prescribing prophylactic antiepileptic drugs and regular use analgesics. Protocol-mandated assessments will be performed according to the schedule (Table 1), and the study flow chart illustrates key steps in the trial (Fig. 1).

**Table 1 Tab1:** Visit and assessment schedule

Items	Screen	Day 1	Day 7 ± 1	Day 14 ± 1	Day 28 ± 3	Day 90 ± 7	Day 180 ± 7
Informed consent	×						
Inclusion/exclusion^a^	×						
Filling general information	×						
Collect medical history	×						
Concomitant medications^b^	×	×	×	×	×		
Physical examination	×						
Surgery		×	×	×	×	×	×
Neurological symptoms^c^	×	×	×	×	×	×	×
Haematoma volume^c^	×			×	×	×	
mRS^c^	×				×	×	×
ADL-BI					×	×	×
Blood routine	×	×		×	×		
Biochemistry	×	×		×	×		
Coagulation	×	×		×	×		
Vital signs^c^	×	×	×	×	×		
Electrocardiography	×			×	×		
Adverse events		×	×	×	×	×	×
Allocate random number	×						
Drug recycling^d^	×	×	×	×	×		

*ADL-BI* activities of daily life on the Barthel Index, *mRS* modified Rankin scale

^a^Accreditation of laboratory examination within 3 days, including head CT, before enrolment

^b^Combined use of drugs before commencing study treatment and continue until the end of the 28-day treatment period

^c^During conservative treatment, if a participant’s neurological function deteriorates associated with an increase in the size of the haematoma and risk of cerebral herniation, they must change over to surgical treatment

^d^Remaining drugs are to be recycled

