### Sample size {14}

We estimate a sample size of 240 patients will provide 90% power to detect a treatment effect of 20% absolute improvement in the primary composite good outcome, after considering a 5% loss-to-follow-up at 4 weeks, then 240 patients in total with 120 per group is needed to be recruited for this study and good outcome in the single atorvastatin control group of 62.6% being consistent with the single atorvastatin group of the ATOCH trial (48 of 81) [15], a pilot trial showing 20 of 30 patients had a good outcome in a single atorvastatin group [23] and medical record data showing 9 of 12 patients had a good outcome at a single centre in 2017 [17]. The combined drug treatment effect was assumed to be consistent with the percentage of good outcomes found in 29 of 30 patients in a pilot clinical trial [23] and 95 of 108 patients’ medical records from our single centre showing a good outcome.

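### Volume reduction and the 28-day Barthel score are compared by tests that take no baseline covariate, which costs efficiency in secondary outcomes but not validity; text and Table 1 also disagree on a pre-treatment Barthel score

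*Protocol article*

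**What the plan says.** All references are to the Protocol article.

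- **Primary outcome, section {20a}:** a chi-square test and a logistic regression adjusted for site, age, sex and baseline haematoma volume.
- **Secondary outcomes, same section:** Student's t-test is one option, and "non-parametric Wilcoxon tests will be performed for continuous outcomes and the chi-square test for dichotomous outcomes". For the mRS, "Ordinal logistic regression will be used for the analysis of the shift in the full range of scores on the mRS"; no covariate is listed.
- **Outcomes {12}:** the continuous secondary outcomes are the reduction in haematoma volume at 14, 28 and 90 days and the ADL-BI at 28 days. Volume is thus expressed relative to baseline; ADL-BI is a follow-up score.
- **Schedule, Table 1 ("Visit and assessment schedule"):** haematoma volume and mRS are marked at screening. ADL-BI is marked only at days 28, 90 and 180.
- **Concomitant care {11d}:** "mRS and ADL-BI were scored before treatment and at the end of 4 weeks, 3 months and 6 months". This gives ADL-BI a pre-treatment measurement that Table 1 does not show.

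**The concern.** The paragraph that treats baseline volume, age, sex and site as worth adjusting for in the primary outcome sets them aside for the continuous secondary outcomes. How far a haematoma can shrink depends on its starting size, and function at 28 days depends on function before treatment. A t-test or Wilcoxon test cannot take such a variable as a covariate; for volume, baseline enters only by subtraction. If the baseline value predicts the outcome, the plan gives away precision that needs no further data for volume and mRS.

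The disagreement over ADL-BI bears on the same point. If the schedule in Table 1 is what sites follow, a pre-treatment Barthel score will be missing for some or all patients and cannot be recovered later.

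**Working it through.** **1. The plan's own figure.** Inputs from Sample size {14}: "90% power to detect a treatment effect of 20% absolute improvement in the primary composite good outcome", "good outcome in the single atorvastatin control group of 62.6" per cent, and "after considering a 5% loss-to-follow-up at 4 weeks". From {20a}: "All statistical tests are two-sided, with a *p*-value < 0.05 indicating statistical significance". The control rate is (48 + 20 + 9)/(81 + 30 + 12) = 77/123 = 62.6%, so the intervention rate is 82.6%.

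n per arm = [1.960 × √(2 × 0.726 × 0.274) + 1.282 × √(0.626 × 0.374 + 0.826 × 0.174)]² / 0.20², rounded up to 103, or 113 with a continuity correction. Dividing 113 by 0.95 gives 119 per arm, 238 in total, against the stated 240. Without the correction the total is 218. The article does not say which formula was used, but 240 is adequate for the primary outcome. It gives no power or precision figure for volume or ADL-BI.

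**2. Variance of the treatment difference.** Let r be the correlation between the baseline covariate and the follow-up value. The article gives none, so r is assumed. For volume, assume equal SDs at baseline and follow-up. Relative to a t-test on follow-up values alone:

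- change score: 2(1 − r)
- ANCOVA on baseline: 1 − r²
- ANCOVA relative to change score: (1 − r²) / [2(1 − r)] = (1 + r)/2

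The equal-SD assumption affects the size, not the direction. With SDs s₀ and s₁, the change-score variance exceeds the ANCOVA variance by an amount proportional to (s₀ − r·s₁)², which is never negative.

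**3. The right benchmark for each outcome.** Reading volume reduction as a continuous change from baseline, its comparator is the change score. For 28-day ADL-BI it is the follow-up-only test.

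| Assumed r | Volume: (1 + r)/2 | Variance cut | ADL-BI: 1 − r² | Variance cut |
|---|---|---|---|---|
| 0.3 | 0.65 | 35% | 0.91 | 9% |
| 0.4 | 0.70 | 30% | 0.84 | 16% |
| 0.5 | 0.75 | 25% | 0.75 | 25% |
| 0.8 | 0.90 | 10% | 0.36 | 64% |

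The two columns move in opposite directions: for volume the gain shrinks as r rises, for ADL-BI it grows. The last ADL-BI entry only completes the formula; a correlation that high is not claimed.

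**4. What this means for power.** Take 120 × 0.95 = 114 per arm and an effect of (1.960 + 0.842) × √(2/114) = 0.371 follow-up SD, which a follow-up-only t-test detects with 80% power.

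| Assumed r | Change score | Follow-up only | ANCOVA |
|---|---|---|---|
| 0.3 | 66% | 80% | 84% |
| 0.5 | 80% | 80% | 90% |
| 0.8 | 99.3% | 80% | 99.7% |

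For volume compare the second column with the last; for ADL-BI, the third with the last.

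**5. The ADL-BI schedule.** Section {11d} puts ADL-BI and mRS together as scored before treatment. In Table 1 the mRS row has a screening mark and the ADL-BI row directly below has none, while their marks at days 28, 90 and 180 coincide. The rows line up, so a table-reading fault is unlikely. The two statements cannot both describe the schedule.

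**The case against.** The strongest reply is that the named tests are valid. After 1:1 randomisation an unadjusted comparison is unbiased in expectation and keeps its type I error, which already allows for chance imbalance. Because allocation is unstratified (Trial design {8}), a reader might infer that baseline imbalance undermines these comparisons. The article does not support that: only efficiency is lost. This part of the reply stands.

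Second, volume already uses baseline by being a reduction. That is correct, and it is why 1 − r² is the wrong benchmark for volume. It does not remove the point, since subtraction fixes the baseline slope at 1 whereas ANCOVA estimates it.

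Third, a reader might extend the criticism to the mRS. Ordinal logistic regression accepts covariates, the article does not call the model unadjusted, and listing covariates is commonly left to an analysis plan, which is not shown. The variance formulas above are also linear-model results; in ordinal logistic regression adjustment mainly raises power rather than narrowing the standard error. No finding is made on the mRS.

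Fourth, ADL-BI is a bounded score in patients selected for pre-morbid independence, so a rank test is defensible and linear ANCOVA is not plainly better. This stands and shapes the fix.

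Fifth, a reader might conclude that no baseline ADL-BI exists. Section {11d} says it was scored, the case report form is not shown, and the planned outcome is the 28-day score rather than a change. The documents establish an inconsistency, not a loss of data.

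**Conclusion.** The point holds as one of efficiency. For volume reduction at three time points and ADL-BI at 28 days, the article fixes tests that take no covariate although a suitable baseline variable is scheduled for every patient. The direction is secure for volume; the size depends on assumed correlations. The variance given away is 35% to 10% for volume over r = 0.3 to 0.8 with equal SDs, and 9% to 25% for ADL-BI over r = 0.3 to 0.5. For ADL-BI, r is the correlation with whichever covariate is used, and the figure is only a guide if a rank-based or ordinal model is chosen.

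There is no bias and no inflation of type I error, and neither the primary analysis nor the sample size is touched. The conflict between section {11d} and Table 1 over pre-treatment ADL-BI is a separate, definite inconsistency.

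**What to change.** 1. **Volume.** Before unblinding, make the main analysis at each time point an ANCOVA, or a mixed model across visits, adjusted for baseline volume, site, age and sex, matching the primary model. Keep the t-test or Wilcoxon test as support.
2. **ADL-BI at 28 days.** Adjust for one covariate scheduled for all patients: the pre-treatment mRS at screening. Do not use baseline ADL-BI for some patients and mRS for others, which would mix two scales in one covariate. If the score is strongly skewed, use a rank-based or ordinal model.
3. **Schedule.** Reconcile section {11d} with Table 1, and state whether a pre-treatment ADL-BI was collected and for whom. If it is intended, mark it at screening for patients still to be enrolled. Trial status reports 141 enrolled as of 7 November 2021, so at that date this could help at most 240 − 141 = 99 patients.

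The cost is wording in the analysis plan and, if item 3 is resolved that way, one short scale that the text already reports as done. The volume model needs no new data. With 14 centres it estimates about 18 parameters (intercept, treatment, 13 site terms, age, sex, baseline volume), leaving 228 − 18 = 210 residual degrees of freedom when 114 per arm are followed, so adjusting for site costs little.
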